## Abstract

**Background:**

Childhood obesity frequently persists into adulthood and is associated with an increased risk and earlier onset of cardiovascular disease in later life. Behavioral change strategies have been proposed as the first-line weight management approach for children and adolescents with obesity. Nonpharmacological interventions, such as traditional Chinese medicine (TCM) auricular acupressure treatment and intermittent low-carbohydrate diet (ILCD), are increasingly being investigated in the young obese population. However, there is limited high-quality evidence about effectiveness and safety in weight control and reducing cardiometabolic risk in the pediatric population.

**Objective:**

This study aimed to compare the effect of cardiometabolic risk reduction between TCM auricular acupressure treatment (TAAT) and ILCD in children with overweight or obesity with gastric-heat and dampness-obstruction syndrome.

**Methods:**

This is a randomized controlled trial. Eligible participants are children with overweight or obesity and enrolled at the obesity clinic of the department of TCM at a tertiary children’s hospital. Eligible participants must meet the following criteria: (1) be aged between 6 and 18 years, (2) be overweight, and (3) have gastric-heat and dampness-obstruction syndrome. Recruited children will be randomized 3:1 to receive either TAAT or a self-administered ILCD for 1 month: 150 in the TAAT group and 50 in the ILCD group. The primary outcome is the change in body weight from the beginning of treatment to the end of 1 month. Secondary outcomes included body weight, waist circumference, waist-to-height ratio, BMI, blood pressure, body fat content, indexes of liver and renal function, indexes of glucose metabolism, gut microbiota, and TCM syndrome scores at the end of 1 month and 3 months, respectively. Primary statistical analyses were conducted using the intention-to-treat strategy. A generalized linear model was used to compare the difference in weight change between the groups, with the baseline body weight as the covariate, to obtain the estimate of the mean difference in body weight change and its 95% CI, using Gaussian for family function and identity for link function.

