**Results:**

The study protocol was approved by the institutional ethical committee and registered on ClinicalTrials.gov on May 5, 2023, before recruitment. Recruitment began in June 2023 and is expected to be completed by December 2025. As of November 2024, we have enrolled 112 participants.

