### Sample Size

The primary outcome was the change in body weight from baseline to 1 month. The sample size calculation was based on the difference in weight change between the 2 groups: the TAAT group and the ILCD group.

Our pilot data from 12 patients revealed a weight loss of 1.9 kg after 4 weeks of TAAT and a weight reduction of 1.4 kg after 4 weeks of ILCD, with an SD of 1.1 kg. We assumed a 0.5 kg difference in weight reduction between the 2 arms, power of 0.80, a 2-sided α of .05, and a sample size ratio of 3:1, a minimum sample size of 150 for the TAAT group and 50 for the ILCD group were required, respectively. Assuming a dropout rate of 15%, the trial enrolled at least 240 participants. The “test for 2 means module” of the PASS 16.0 software was used.

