### Recruitment

The estimated period for recruitment, intervention, and data collection would take probably 30 months to complete. Eligible clients attending the obesity clinic at the Children’s Hospital of Fudan University were invited to participate in the study through collaboration with TCM clinicians. The time required for participant recruitment and baseline assessment was approximately 30 to 45 minutes.

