## Results

The protocol was registered on ClinicalTrials.gov (NCT05847478) on May 5, 2023. The current protocol is version 2.0, dated February 28, 2023, which is the final version as approved by the institutional ethical committee. Recruitment started in June 2023 and is expected to be completed in December 2025. By November 2024, we had enrolled 112 participants (Figure 3).

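### The Abstract gives 200 as the number randomised, while the Sample Size section treats 200 as the pre-dropout minimum and sets enrolment at 240 or more; at the protocol's own 15% loss the two differ by about 8 points of power

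*Protocol article*

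**What the plan says.** The Abstract (Methods) describes the children as "randomized 3:1 to receive either TAAT or a self-administered ILCD for 1 month: 150 in the TAAT group and 50 in the ILCD group". That is a total of 200 randomised.

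The Sample Size section uses the same pair of numbers differently. It states its inputs ("We assumed a 0.5 kg difference in weight reduction between the 2 arms, power of 0.80, a 2-sided α of .05, and a sample size"), allocates 3:1, and draws on pilot figures that include "a weight reduction of 1.4 kg after 4 weeks of ILCD, with an SD of 1.1 kg". From these it concludes that "a minimum sample size of 150 for the TAAT group and 50 for the ILCD group were required, respectively". The next sentence adds the allowance for loss: "Assuming a dropout rate of 15%, the trial enrolled at least 240 participants".

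On timing, the Abstract (Results) says: "Recruitment began in June 2023 and is expected to be completed by December 2025. As of November 2024, we have enrolled 112 participants". The main Results section repeats the dates: "Recruitment started in June 2023 and is expected to be completed in December 2025". The Recruitment section says: "The estimated period for recruitment, intervention, and data collection would take probably 30 months to complete".

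**The concern.** The same 150 and 50 serve as the number randomised in one place and as the number needed before dropout in another. The resulting enrolment targets are 200 and at least 240, which is 40 children apart.

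Power depends on how many children have the 1-month weight. If enrolment closed at the Abstract's figure and losses ran at the rate the protocol assumes, the primary comparison would have less than the stated 80% power for 0.5 kg, and a null result would be harder to interpret. Enrolment was still open when the article was written, so the number that closes it should be settled before closure.

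**Working it through.** **Inputs (Sample Size section).** Difference d = 0.5 kg, SD s = 1.1 kg, two-sided level 0.05, power 0.80, ratio 3:1, dropout 15%.

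**Step 1: reproduce the plan's figure.** With n children in the ILCD arm and 3n in the TAAT arm, the normal approximation gives

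n = (1 + 1/3) × (s/d)² × (1.96 + 0.8416)² = (4/3) × (1.1/0.5)² × (2.8016)² = 50.65.

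Rounded up, this is 51 and 153, or 204 in all. The plan's 50 and 150 are within 3% of that. The power of 150:50 is 79.5% by the normal approximation and 79.1% by the noncentral t, so the stated minimum is reproduced within rounding.

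**Step 2: allowance for loss.** 200/0.85 = 235.3, so 236. 204/0.85 = 240. Either route is compatible with a target of at least 240.

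**Step 3: power under each target.** Noncentral t with noncentrality d / (s × √(1/n + 1/(3n))), evaluable children split 3:1:

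| Randomised | Loss at 1 month | Evaluable | Power for 0.5 kg |
|---|---|---|---|
| 240 | 15% | 204 | 79.9% |
| 200 | 15% | 170 | 72.3% |
| 200 | 10% | 180 | about 75% |
| 200 | 5% | 190 | about 77% |
| 200 | none | 200 | 79.1% |

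At the protocol's own dropout rate the gap is 79.9 − 72.3 = 7.6 points. The chance of missing a true 0.5 kg difference rises from about 20% to about 28%.

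**Step 4: accrual, as a note only.** The article reports 112 enrolled by November 2024 after a June 2023 start, which is about 17 to 18 months:

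- Average pace: 112/18 = 6.2 to 112/17 = 6.6 per month.
- Projection to December 2025: 112 + 12 × 6.22 = 187 at the low end, 112 + 14 × 6.59 = 204 at the high end, and about 195 centrally. The spread comes from how months are counted.
- At 195 enrolled and 15% loss: 195 × 0.85 = about 166 evaluable, power about 71%, and 0.56 kg detectable at 80%.
- Pace needed to reach 240 with 13 months left: (240 − 112)/13 = 9.8 per month.
- Total time to 240 at the average pace: 240/6.59 = 36 to 240/6.22 = 39 months.

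**The case against.** The best reply is that the Sample Size section is the operative text and already sets a floor of 240. The Abstract is condensed and probably repeats the pre-dropout figure, and the article nowhere says that enrolment stops at 200. That is a fair account of how the mismatch arose. It does not remove it, because the Abstract states those numbers as randomised.

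A second reply is that 72% needs the full 15% to be missing at 1 month. The Sample Size section does not say to which visit the 15% applies. The Follow-Up Period section defines a dropout as someone not reached for 3 months and keeps the data of those who withdraw. Loss at the primary endpoint could therefore be smaller, which is why the power is shown over a range. The primary model also adjusts for baseline weight, which may recover some power by an amount that cannot be computed from the article.

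Four stronger readings are tempting, and the document does not support them:

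- *Only 240 delivers 80% power.* Power follows the evaluable number. With complete data 200 gives 79.1%, and enrolling 236 would also leave 200 evaluable after 15% loss.
- *The sample size calculation is wrong.* It reproduces within rounding. Whether 240 came from 204/0.85 or from rounding 236 up is conjecture and does not matter.
- *Reported accrual falls short at about 195.* The article reports only the single count of 112. The 195 is a straight-line projection that carries any slow start forward unchanged. It is a forecast, not a contradiction.
- *Recruitment must close around September 2025.* This would follow if the 30 months had to hold the last 3-month visit. That sentence is an explicit estimate, whereas both statements of the end of recruitment give December 2025, and the primary endpoint needs only 1 month of follow-up.

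**Conclusion.** The point holds as an internal inconsistency in the enrolment target. The Abstract's 200 randomised and the Sample Size section's 240 or more cannot both be the target, and the article does not reconcile them. On the protocol's own inputs, including its 15% loss, the Abstract's figure gives about 72% power and the Sample Size section's about 80%. With lower loss at 1 month the shortfall shrinks, and it nearly disappears with complete data.

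These figures assume SD 1.1 kg, a realised 3:1 split and no gain from baseline adjustment. The inconsistency threatens power and clarity. It introduces no bias and changes neither the estimand nor the analysis.

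The accrual projection is secondary. Every value in its range (187 to 204) is well below 240, so the stated end date and the stated target sit uneasily together, but only on the assumption of an unchanged pace.

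**What to change.** State one enrolment target wherever a number appears: at least 240 randomised. Label 150 and 50 as the evaluable minimum and correct the Abstract. If arm sizes are given for 240, describe 180:60 as the expected split, because the Randomization and Blinding section specifies simple randomisation, which does not fix the arm totals. It would also help to say that the 15% refers to the 1-month weight, if that is what was meant.

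Then align the timeline in one of two ways. Either restate the recruitment end date, since at the average pace 240 would take about 36-39 months from June 2023. Or keep December 2025 and state what it is expected to deliver: about 195 enrolled, about 166 evaluable at 15% loss, about 71% power for 0.5 kg, or 0.56 kg detectable at 80%, marked as a projection. The 30-month sentence should say whether it covers follow-up of the last participant.

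The cost is wording only. Nothing is asked beyond the 240 already stated, although a published date or power may become less favourable. The registry entry cannot be seen here and should be checked for the same mismatch.

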**Results:**

The study protocol was approved by the institutional ethical committee and registered on ClinicalTrials.gov on May 5, 2023, before recruitment. Recruitment began in June 2023 and is expected to be completed by December 2025. As of November 2024, we have enrolled 112 participants.

**Conclusions:**

This randomized controlled trial will provide evidence on the treatment effects and safety of TAAT versus ILCD among children with overweight or obesity with gastric-heat and dampness-obstruction syndrome, in reducing body weight and improving cardiometabolic risks. Exploratory aims include potential underlying mechanisms of the 2 kinds of interventions, based on biosamples.

**Trial Registration:**

ClinicalTrials.gov NCT05847478. https://clinicaltrials.gov/study/NCT05847478

**International Registered Report Identifier (IRRID):**

DERR1-10.2196/59856

## Introduction

The Report on Cardiovascular Health and Disease in China (2022) [1] shows that cardiovascular disease is the leading cause of death among urban and rural residents in China, which is mainly caused by hypertension, dyslipidemia, diabetes, overweight or obesity, physical inactivity, inappropriate diet, and metabolic syndrome. It is important to note that obesity, especially abdominal obesity, is a direct risk factor for cardiovascular disease. Unfortunately, obesity can persist from childhood and adolescence into adulthood [2,3]. Obesity in children and adolescents is a global health issue [4], with China, India, the United States, Indonesia, and Brazil being the top-ranked countries, each estimated to have more than one million children with obesity in 2030 [5].

First-line treatments for obesity should be supported by behavioral change strategies [4]. Family-based interventions that address diet, physical activity, sedentary behavior, and sleep quality are recommended. However, the weight loss effect is not ideal and is difficult to maintain. Although evidence for pharmacotherapy and bariatric surgery as supplemental therapies is emerging, they are not recommended for weight loss in children [6]. In fact, safer and more acceptable nonpharmacological interventions, such as traditional Chinese medicine (TCM) and TCM auricular acupressure treatment (TAAT), are increasingly used.

The earliest known mention of TAAT dates back to Huang Di Nei Jing (circa 100 BC) [7,8]. Currently, auricular therapy is widely used in clinical settings for pain relief, epilepsy treatment, improving sleep quality, and obesity [9-11]. This approach offers the advantage of individualized treatment based on the dialectical theory of governance. TAAT has been found effective on children, adolescents, and adult obesity [12-14]. The study found that auricular acupuncture stimulation clearly modulates the feeding-related hypothalamic neuronal activity of experimental (both hypothalamic and dietary) obese rats. The results suggest that auricular acupuncture stimulation may not reduce appetite but is more likely concerned with satiation formation and preservation [15]. However, high-quality clinical evidence is lacking. According to TCM, obesity is located on the spleen and stomach, followed by the liver and kidney. TCM identifies several syndrome types of obesity, including gastric-heat and dampness-obstruction syndrome, spleen-deficiency and dampness-stagnation syndrome, liver-qi stagnation syndrome, and spleen-kidney deficiency syndrome [16,17]. Among these, gastric-heat and dampness-obstruction syndrome is the most common type [18]. In order to ensure the sample size is attained, the gastric-heat and dampness-obstruction syndrome has been selected for inclusion in the study. In addition, the choice of a single syndrome in preference to multiple options ensures comparability in the evaluation of efficacy between groups.

Numerous studies have demonstrated the effectiveness of low carbohydrate diets (<50 g per day or <10% energy from carbohydrates) in combating obesity [19], deemed feasible and acceptable [20,21]. Our previous research has shown that the intermittent low carbohydrate diet (ILCD) was effective in improving weight-related outcomes in children and adolescents [22]. However, the efficacy needs to be further investigated, and long-term effects are uncertain. So far, there are currently no randomized controlled trials comparing the effectiveness between ILCD and TAAT. At the same time, our secondary aim is to explore the mechanistic differences between the 2 nondrug interventions. Therefore, this study aims to assess whether TAAT as the experimental arm is more effective than ILCD as the control arm in improving the cardiometabolic risk in children with overweight or obesity with gastric-heat and dampness-obstruction syndrome.

## Methods

### Objective and Trial Design

This is a randomized controlled superiority trial that aims to compare the effects of TAAT versus ILCD in reducing the cardiometabolic risk in children with overweight or obesity with gastric-heat and dampness-obstruction syndrome. Participants were allocated in a 3:1 ratio to either an auricular acupressure treatment group or a control group. The TCM clinicians were aware of the allocation but did not participate in the following research. Conversely, the outcome observers were blinded about the allocation.

### Recruitment and Study Setting

Eligible participants were recruited by a pediatrician at the obesity clinic of the Department of TCM in Children’s Hospital of Fudan University. All participants were required to provide written consent before intervention.

### Participants Eligibility Criteria

Eligible participants must meet the following criteria: (1) be aged between 6 and 18 years, (2) be overweight [23], and (3) have gastric-heat and dampness-obstruction syndrome [16].

Overweight or obesity with gastric-heat and dampness-obstruction syndrome was defined as follows:

(1) The “Expert Consensus on Diagnosis, Assessment, and Management of Obesity in Chinese Children” states that BMIs between 85% and 95% were classified as overweight, while those above 95% were classified as obese for children of the same gender and age [23].

(2) The “Pediatrics of Traditional Chinese Medicine” framework [16] outlined the conditions that must be met for the gastric-heat and dampness-obstruction syndrome, which include (1) dizziness and heaviness in the head, (2) thirst, (3) rapid digestion of food and polyorexia, (4) heaviness of limbs, (5) fatigue body and lack of strength, (6) a red tongue, (7) greasy fur, and (8) a slippery pulse. It is important to note that conditions (7) and (8) must be satisfied, while conditions (1) to (6) must be satisfied at least 3 conditions.

Participants who met any of the following exclusion criteria were excluded: (1) having hereditary obesity or obesity caused by endocrine disorders, such as Cushing syndrome, primary hypothyroidism, and hypothalamic obesity; (2) currently being enrolled in other clinical trials or having participated in another clinical trial in the past 3 months; (3) self-administration of oral weight-loss medications or other forms of meal replacements; and (4) having serious organic diseases of the heart, liver, kidneys, or brain, or infectious diseases or psychiatric disorders.

### Interventions

#### Experimental Group (TAAT Group)

Specialized TCM clinicians conducted TAAT following a standardized procedure. The location and operation of the ear acupoints followed the guidelines outlined in the “National Standard of the Peoples Republic of China for Nomenclature and Location of Auricular Points (GB/*t* 13734-2008).” In addition, all TCM clinicians had received specialized training to ensure a comprehensive understanding of the auricular acupressure intervention program and to standardize the procedures performed by different clinicians.

The study selected the following ear acupoints for acupressure treatment: Shenmen (TF4), Xiaoping (TG2), Endocrine (CO18), Stomach (CO4), Mouth (CO1), and Subcortex (AT4) (refer to Figures 1 and 2) [24]. The acupressure was administered using an opaque patch with Vaccaria seed. Participants were instructed to apply pressure for 1 minute before and after meals each day, for a total of 2 to 3 days per week. They were followed weekly and received a 3-course treatment, with 1 course per month.

**Figure 1 figure1:**
[figure not shown]
Location of the subcortex (AT4).

**Figure 2 figure2:**
[figure not shown]
Location of the shenmen (TF4), Xiaoping (TG2), endocrine (CO18), stomach (CO4), mouth (CO1).

#### Control Group (ILCD Group)

Participants were required to limit their daily carbohydrate intake to 50 g or less, while their dietary calorie intake was not restricted for nonconsecutive 7 days of 2 weeks, corresponding to 14 days in a month. On the remaining days, participants should maintain their normal diet. The intervention period lasted for 1 month, followed by a 2-month follow-up period [20].

### Follow-Up Period

First, a WeChat group was created for parents of participants to facilitate communication and monitoring about diet and exercise recording, as well as scheduling follow-up appointments. Second, adherence to the study interventions were uniformly assessed in both groups at each visit. Third, if participants missed any visits, investigators would contact them directly by telephone to encourage continued participation and evaluate barriers.

The research assistant attempted to establish contact with the missed participants. A dropout participant was defined as someone who had not been reached for 3 months. If participants decided to withdraw before completion, all collected data would be remained for analysis.

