#### Dietary and Exercise Data

Diet and exercise data were recorded by the children and their families, but they were educated by qualified clinicians before recording [26,27].

(1) **From the baseline to the first month:** The weight of the food was measured using an electronic scale before and after each meal, and photographs were taken as well. Participants were required to wear sports watches every day, including during sleep, but not while bathing, swimming, or in other special cases. Dietary data included the type and weight of the foods consumed, while exercise data included step count, calorie consumption, resting heart rate, sleep duration, and exercise type. All data was meticulously recorded daily in the “Diet and Exercise Handbook.”

(2) **From the second month to the third month:** The method and content remained unchanged. Dietary and exercise data were recorded on Thursdays, Fridays, and Saturdays during 1 week, and distributed at the beginning, middle, and end of the month, rather than every day.

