### Randomization and Blinding

Participants were randomly assigned to either the experimental or control group through a simple randomization process generated by the R Language (version 4.2.2; R core team). This process was designed by the clinical trial unit of the Children’s Hospital of Fudan University and follows a 3:1 allocation ratio.

The study coordinator, who was not involved in data collection, performed the allocation. The randomization list was kept strictly confidential. Allocation was done by the study coordinator in a sequentially numbered fashion using identical, opaque, sealed envelopes. The recruiting clinicians were blinded to study group allocation and did not have access to the allocation sequence.

Eligible participants were enrolled by trained clinicians. The study coordinator independently assigned participants to either the intervention or control groups. Outcome observers were blinded. The analysis team received aggregated data obtained for the control and experimental groups. Study participants could be blinded, but they were scheduled for separate follow-up dates.

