## Discussion

### Anticipated Findings

It is hypothesized that TAAT will prove superior to ILCD in controlling body weight through this clinical trial. In addition, it is anticipated that the mechanistic differences between the 2 nondrug intervention methods will be elucidated. This study will be the first randomized controlled trial to investigate the effect and safety of TAAT compared with ILCD for overweight or obesity and other cardiometabolic risk factors. Previous studies on the effects of auricular treatment have mainly focused on adolescents and adults [12,14]. A study was conducted as a randomized controlled trial to examine the effects of auricular acupressure on obesity improvement in children. However, this trial had a small sample size and did not take into account the impact of diet, exercise, and lifestyle on body weight [15]. Consequently, there is a lack of high-quality clinical trials on the effects of TAAT in children with obesity, although we found some clinical evidence of this approach in children. Furthermore, the participants’ gut microbiota will be studied in order to explore the underlying mechanisms of the 2 different interventions.

All participants in this study are patients from the Department of TCM and seeking TCM intervention. As one of the treatment methods in TCM, previous studies have shown that TAAT is effective in reducing body weight, WC, and body fat mass [14,29]; therefore, we did not consider a blank control group, instead, using an ILCD, according to its effect indicated in recent randomized trials [30,31].

TAAT appears minimal side effects, including the pain caused by local noninvasive stimulation that can be tolerated by most children [32]. As participants are recruited from the obesity clinic of the Department of TCM, randomization is set in a 3:1 ratio, allowing that needs of more participants are satisfied.

Maintaining compliance remains challenging to the young population. To ensure better compliance, we use methods such as regular reminders and random checks. To avoid bias, the outcome observer is unaware of the grouping of the participants.

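### The Follow-Up Period section describes one WeChat group for participants' parents with no split by arm, which exposes the comparison to cross-arm contamination

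*Protocol article*

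**What the plan says.** All references are to the protocol article.

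- **Parent channel (Follow-Up Period).** "a WeChat group was created for parents of participants to facilitate communication and monitoring about diet and exercise recording". The group also serves to schedule follow-up visits. The wording is singular and mentions no division by arm. The next sentence says that "adherence to the study interventions were uniformly assessed in both groups at each visit", so the authors name the arms when they mean them.
- **Separation of participants (Randomization and Blinding).** "Study participants could be blinded, but they were scheduled for separate follow-up dates". No reason is given for the separate dates, but this is the only stated step that could keep the arms apart.
- **Delivery of the diet (Abstract, Methods).** Children "receive either TAAT or a self-administered ILCD for 1 month".
- **Delivery of acupressure (Experimental Group).** "Specialized TCM clinicians conducted TAAT following a standardized procedure", at six named ear points. The participant's own part is the pressing: "Participants were instructed to apply pressure for 1 minute before and after meals each day".
- **What families came for (Anticipated Findings).** "All participants in this study are patients from the Department of TCM and seeking TCM intervention".
- **Diet data up to month 1 (Dietary and Exercise Data).** "The weight of the food was measured using an electronic scale before and after each meal, and photographs were taken as well". Records are kept daily in a handbook.
- **Analysis (Statistical Analysis).** Intention-to-treat is primary, with a per-protocol sensitivity analysis.

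**The concern.** The trial compares two behavioural treatments that families carry out largely at home. A shared parent chat whose declared subject includes diet recording is a natural place for TAAT parents to learn what the control families are doing. Scheduling messages may reveal the arm as well, because weekly follow-up is stated for TAAT and not for ILCD.

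The two directions of cross-use have opposite effects:

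- TAAT families who add low-carbohydrate days could increase weight loss in the TAAT arm. The effect of the diet would then be credited to acupressure, in favour of the superiority hypothesis.
- ILCD families who obtain acupressure would narrow the difference and cost power.

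Under intention-to-treat both enter the primary estimate. The aim of finding mechanistic differences between the two treatments would be blurred in the same way. The article states no rule or check on use of the other arm's intervention during the trial.

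**Working it through.** **Inputs (Sample Size section):** pilot losses 1.9 kg (TAAT) and 1.4 kg (ILCD), difference 0.5 kg, SD 1.1 kg, two-sided α 0.05, power 0.80, ratio 3:1, 150 and 50 children, 15% dropout, at least 240 enrolled. The documents give no contamination rate, so every rate below is an assumption.

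**1. The plan's own figure.** ILCD n = (1.96 + 0.8416)² × 1.1² × (1 + 1/3) / 0.5² = 7.849 × 1.21 × 1.333 / 0.25 = 50.7, so 51, with 153 for TAAT, total 204. Then 204 / 0.85 = 240. The stated 150, 50 and 240 reproduce, and there is no arithmetic error.

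**2. Power with no contamination.** SE = 1.1 × √(1/150 + 1/50) = 0.180 kg, and 0.5 / 0.180 = 2.78. Power is 0.791 by the noncentral t (0.795 by the normal approximation). Dropout is the only allowance made, so there is no spare power.

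**3. Dilution (less likely route).** If a fraction c of ILCD children add acupressure and reach the TAAT mean, the difference becomes 0.5 × (1 − c).

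| Assumed net dilution | Difference (kg) | Power at 150 v 50 | Evaluable N for 80% power |
|---|---|---|---|
| 0% | 0.50 | 0.791 | 204 |
| 10% | 0.45 | 0.703 | 252 |
| 20% | 0.40 | 0.601 | 320 |

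Ten per cent of 50 is 5 children.

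**4. Inflation (likelier route).** Suppose 10% of TAAT children (15 of 150) add the diet and each loses an extra 0.7 to 1.4 kg, that is, half to all of the pilot ILCD loss. The TAAT mean loss rises by 0.10 × 0.7 = 0.07 kg to 0.10 × 1.4 = 0.14 kg, which is 14% to 28% of 0.5 kg. If the true difference were zero, the chance of wrongly declaring TAAT superior would rise from 2.5% to 1 − Φ(1.96 − 0.07/0.180) ≈ 6%, up to 1 − Φ(1.96 − 0.14/0.180) ≈ 12%. The upper end is generous: 1.4 kg is a loss from baseline, with no untreated comparison, and may not add in full to TAAT.

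**5. Both together.** At 10% in each arm, the net shift is 0.07 − 0.05 = +0.02 kg to 0.14 − 0.05 = +0.09 kg. Other pairs of rates can make it negative, so the arithmetic does not fix the direction.

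**6. What can still be protected.** Enrolment was 112 by November 2024. Of at least 240 planned, 240 − 112 = 128 (53%) were still to come.

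**The case against.** The strongest reply is that the text is being over-read. It does not say that both arms share the group, that parents may post freely, or that treatment is discussed there. A scheduling channel combined with separate follow-up dates fits arm-specific groups too, and an article may leave the set-up of a chat group to the full protocol. Food data go into a handbook, and nothing says they are posted to the chat. The adherence checks, the daily weighed and photographed food records and the per-protocol analysis would help to reveal cross-use. The membership rules of the per-protocol set normally belong in the SAP.

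Much of this stands:

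- A reader might infer that the trial's contrast is already contaminated. The documents do not support that: none is reported and the size is unknown.
- A reader might infer that both treatments are equally easy to copy. They are not: trained clinicians place the seeds, so copying into the ILCD arm is harder.
- A shared group is the natural reading of the singular wording, not an explicit statement.
- The absence of per-protocol rules is not itself a fault here.

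What remains is that the article does describe the channel, in the singular and without a split, next to a sentence that does distinguish the arms. Diet records could reveal low-carbohydrate days in TAAT children after the event, but they do not prevent them, and the article states no such use of the records.

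**Conclusion.** The point holds as an exposure to contamination, not as contamination shown. On its plain reading, the single parent group works against the only stated separation of the arms. The likelier cross-use, the self-administered diet taken up in the TAAT arm, would favour TAAT; the reverse is less likely and would dilute the difference.

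The size cannot be derived from the documents. An assumed net dilution of 10% or 20% would lower power from about 0.79 to about 0.70 or 0.60. An assumed 10% uptake of the diet in the TAAT arm would overstate its advantage by 0.07 to 0.14 kg, if each such child loses 0.7 to 1.4 kg more. These figures show sensitivity and predict nothing about this trial. The stated sample size is sound on its own inputs and need not change on this ground. If the groups are already separate, one sentence saying so settles the question of the channel.

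**What to change.** 1. Use arm-specific WeChat groups, or one-to-one messages with the coordinator, for current and future participants. If this is already done, say so in the Follow-Up Period section.
2. At the 1-month visit, ask about and record use of the other arm's intervention. Use the daily diet records already collected to detect low-carbohydrate days in the TAAT arm, applying the control diet's own carbohydrate threshold as the definition.
3. Report cross-use by arm, and separately for families enrolled before and after the change.
4. Name cross-use as a prespecified deviation in the per-protocol sensitivity analysis and keep intention-to-treat as primary.

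The cost is one more chat group, one case-report-form question and a pass through diet data already held. The change cannot undo exposure of families already in the group (112 enrolled by November 2024), which is why item 3 splits the report by time of enrolment.
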